#### Secondary outcome measures

Secondary outcomes are the following: percentage of patients readmitted, total number of readmissions and length of hospitalization for all causes during the first year after hospital discharge, all-cause death, all-cause hospital emergency visits, functional capacity (exercise stress test), quality of life (EuroQol5), adherence to CRP (attendance at follow-up visits), adherence to cardiac pharmacological treatment (Haynes-Sackett test), satisfaction with assistance received (questions selected from the local public health department’s questionnaire, Ambulatory Specialized Care 2008 [14]).

### Demographic and clinical measures

Group allocation, sex, age, education level, marital status, living situation, employment status, main diagnosis, diagnostic reason for referral, location, degree of involvement, number of stents, the ejection fraction, comorbidities (Charlson Comorbidity Index), maximum theoretical heart rate, real maximum heart rate, baseline heart rate, chronotropic index, the level reached on the exercise stress test, time to recover initial heart rate (1 and 3 minutes)), level of risk for cardiac rehabilitation, blood tests, cardiac markers (NTproBNP, troponin I), SBP, DBP, BMI, abdominal circumference, Mediterranean diet, depressive symptoms (Yesavage Depression Scale), basic activities of daily living (Barthel Index), tobacco consumption (Fargeström test), compliance with cardiac medication (Haynes-Sackett method), taking sublingual nitroglycerin, physical activity (Caspersen and Powell classification) and return to work.

### Statistical issues

#### Sample size

To ensure a statistical power of 80% in order to detect differences in the contrast of the null hypothesis (H_0_: equal percentages of cardiac readmissions in the two groups) through a two-tailed chi-square test for two independent samples, with a level of significance of 0.05, and assuming that the percentage of cardiac readmissions in the control group is 25% and the percentage in the intervention group is 12%, each group will require 139 patients. Assuming a 5% loss to follow-up, we estimate that 146 patients will be needed in each arm.

#### Data collection and management

We will collect information on outcome at each stage of recruitment, randomization, treatment allocation, follow-up, and analysis in order to report patient flow according to CONSORT guidelines [15]. We will record the number of patients who meet exclusion criteria, the number of patients who qualified for inclusion but who were not willing to participate, the number of patients assigned to the intervention arm, the number of patients assigned to the control arm, the number of intervention visits, the number of patients who provided follow-up data, the number of patients included in the analysis, and the number of withdrawals.

To ensure that clinical data collection forms are accurately entered into databases, we will periodically validate the information collected in the database (detection of missing and out-of-range values). To maintain the confidentiality of the information, all patients will be identified by study numbers.

#### Statistical analysis

Continuous variables will be summarized using means and standard deviations for normal distributions, and by medians and the 25th and 75th percentiles for non-normal distributions. Categorical variables will be summarized using absolute values and relative frequency. We will test for significant differences among the baseline characteristics of the control and intervention groups. For continuous variables, we will use the Student's *t*-test if both sample groups have normal distribution or the Mann–Whitney *U* test otherwise. We will use the *χ*^2^ test to compare categorical variables (or Fisher’s exact test in 2×2 contingency tables where the expected frequencies are lower than 5).

Percentage of patients readmitted for cardiac disease will be analysed through a two-tailed *χ*^2^ test for two independent samples, and time to first hospital readmission for cardiac disease will be analysed as time to event with Kaplan-Meier estimation and Cox proportional regression models. The deaths occurring without hospitalization will be introduced in the survival analysis as censored data. Event or censored times for all patients will be measured from the time of randomization (visit 0). All information available on the primary and secondary end points will be collected until the time of final contact with the patient, including patients lost to follow-up, at which point follow-up will be censored. Survival data will be presented graphically using the Kaplan-Meier method. We will use the log-rank test to compare the survival curves. To estimate the effect size, we will report the unadjusted hazard ratios (HR) and associated 95% confidence intervals (95% CI) obtained in the bivariate Cox proportional regression models.

To establish whether the allocation group is an independent prognostic factor for cardiac readmission, we will adjust for potential confounders in a multivariate analysis. The model will be adjusted with the significant covariates in bivariate analysis or those that were clinically significant. To estimate the effect size, we will report the adjusted hazard ratios (HR) and associated 95% confidence intervals (95% CI) obtained in the multivariate Cox proportional regression models.

Outcomes will be analysed on an intention-to-treat basis. A two-sided α-level of 0.05 will be considered statistically significant. Data will be analysed using IBM SPSS Statistics for Windows v.20 and Stata v.10.

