### Data collection and measures

#### Procedure

Each day, the cardiac nurse and the physiotherapist will check the bed list of patients admitted to the Cardiology Department. They will select the eligible patients after assessing the clinical history and consulting the cardiologist. In the inpatient setting, the cardiac nurse or the physiotherapist will give verbal and written information related to the study to eligible patients and will resolve all the patients’ doubts. These professionals will stress to the patient that the randomization process will decide the group inclusion. Before discharge (visit −1), eligible patients who agree to participate will be asked to give signed informed consent. In this visit, the cardiac nurse will record the following variables: education level, marital status, living situation, employment status and comorbidities (Charlson Comorbidity Index). On discharge (visit 0) the cardiac nurse or the physiotherapist will contact the Clinical Research Unit regarding the randomization process. Once the cardiac nurse or the physiotherapist knows the randomization group, they schedule the patient for the first cardiac nurse visit and for the exercise stress test.

Patients will attend four cardiac nurse visits (visits 1, 2, 3 and 4). During these visits, the cardiac nurse will describe ways of improving cardiovascular risk factors and cardiac medication adherence, and will answer the patients’ questions. The following variables will be recorded: attendance, systolic blood pressure (SBP), diastolic blood pressure (DBP), heart rate, Body Mass Index (BMI), abdominal circumference, Mediterranean diet, depressive symptoms (Yesavage Geriatric Depression Scale), basic activities of daily living (Barthel index), tobacco dependence (Fargeström test), compliance with cardiac medication (Haynes-Sackett test), taking sublingual nitroglycerin, hospital emergency visits, hospital readmissions and mortality. Quality of life (EuroQol5) will be recorded at all visits except visit 3. To address a possible cross-over effect, all patients will be asked to complete a physical activity questionnaire (Capersen and Powell classification) at baseline and in each follow-up visit. This test categorizes physical activity in four levels: sedentary, irregular activity, non-intensive regular activity, and intensive regular activity.

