Additional information will be recorded in the intervention group. Between visits 1 and 2, intervention patients will attend the training sessions. All sessions will be supervised by the physiotherapist. In each session the following values will be compiled: heart rate (initial, maximum, final), oxygen saturation (initial, during session, final), SBP (start, during session, final), DBP (initial, during session, final), degree of dyspnea (initial, final) and the level on the Borg scale. For each patient, the physiotherapist will compile the data from the exercise sessions and the number of physical sessions attended.

The cardiac nurse or physiotherapist will record the cause of withdrawal during the follow-up. The cardiac nurse will collect all data and enter them in a database designed for this study.

Table 1 summarizes the measures and variables according to the timeline.

**Table 1 T1:** Summary of measures and variables according to the timeline

**VISIT**	**−1**	**0**	**1**	**2**	**3**	**4**
**Time (months)**	**−1**	**0**	**1**	**3**	**6**	**12**
**Inclusion/exclusion criteria and informed consent**	X					
**Sociodemographic data** (sex, age, education level, marital status, living situation, employment status) and **comorbidity** (Charlson Index))	X					
**Cardiovascular risk factors** (diet, alcohol, tobacco dependence - Fargeström test - hypertension, diabetes, exercise practice, family heart disease), **dyspnea**, **depressive symptoms** (Yesavage Depression Scale) and **activities of daily living** (Bartel Index)	X		X	X	X	X
**Random allocation**		X				
**Diagnostic reason for referral** (localization, severity, number of stents, ejection fraction)			X			
**Medication prescribed**			X			
**Exercise stress test** (theoretical maximum heart rate, real maximum heart rate, baseline heart rate, chronotropic index, level reached, recovery time of the initial heart rate - 1 and 3 minutes-)			X	X		
**Level of risk for cardiac rehabilitation**			X			
**Control blood test**			X	X		X
**Anthropometric measures** (Body Mass Index, abdominal circumference)			X	X	X	X
**Systolic and diastolic blood pressure** and **baseline heart rate**			X	X	X	X
**Physical activity** (Capersen and Powell classification)			X	X	X	X
**Quality of life** (EuroQol5)			X	X		X
**Cardiac medication adherence** (Haynes-Sackett method) and **taking sublingual nitroglycerin**			X	X	X	X
**Adherence to Cardiac Rehabilitation Program**			X	X	X	X

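### The percentage readmitted, on which the trial is sized, gets only an unadjusted chi-square; a prespecified adjusted risk difference with a confidence interval would be a free, modest improvement

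*Protocol article*

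**What the plan says.** All references are to the protocol article.

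- **Sample size.** The null hypothesis is equal percentages of cardiac readmission in the two groups, to be tested "through a two-tailed chi-square test for two independent samples", "with a level of significance of 0.05", with power of 80%. The assumed percentages are 25% (control) and 12% (intervention). The result is 139 per group, raised to 146 for losses.
- **Statistical analysis, sized outcome.** "Percentage of patients readmitted for cardiac disease will be analysed through a two-tailed" chi-square test for two independent samples. No effect measure or interval is attached to it.
- **Statistical analysis, time to first cardiac readmission.** Kaplan-Meier, log-rank and Cox models are planned: "To estimate the effect size, we will report the unadjusted hazard ratios (HR") with 95% CI. A multivariate Cox model then gives adjusted hazard ratios, also with 95% CI.
- **Procedure and Table 1.** At the pre-discharge visit −1 the nurse records, among other items, "employment status and comorbidities (Charlson Comorbidity Index"). Table 1 places "sex, age, education level, marital status, living situation, employment status" at that same visit. Random allocation is at visit 0.

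**The concern.** The hypothesis, the sample size and the power all belong to one quantity: the share of patients readmitted for cardiac disease within a year. The analysis named for it gives a p-value. The section speaks of estimating effect size twice, and both times the answer is a hazard ratio for another primary measure. A hazard ratio does not say how many percentage points of patients were spared a readmission, which is the scale of the trial's own hypothesis and the more useful one for the health-planning remarks in the Discussion.

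The protocol also wants covariate-adjusted results, but plans them only in the Cox model. Two plausible prognostic variables are in hand before allocation and are not used in the sized comparison. At stake is an estimate on the right scale and a small gain in precision from data already being collected.

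**Working it through.** **1. Reproduce the plan's figure.** Inputs from the Sample size section: p₁ = 0.25, p₂ = 0.12, two-sided α = 0.05, power 80%. With the mean p̄ = 0.185:

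n = [1.96·√(2p̄(1−p̄)) + 0.8416·√(p₁(1−p₁) + p₂(1−p₂))]² / (p₁−p₂)²

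- 2 × 0.185 × 0.815 = 0.30155; its root is 0.5491; × 1.96 = 1.0763
- 0.1875 + 0.1056 = 0.2931; its root is 0.5414; × 0.8416 = 0.4556
- (1.0763 + 0.4556)² / 0.13² = 2.347 / 0.0169 = 138.9, so **139 per group**

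This matches the protocol exactly. Power at 139 per group is 80.0%.

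**2. What an interval would show.** At 139 per group the 95% half-width of the risk difference is 1.96·√(0.2931/139) = 0.090. If the design assumptions come true, the result is 13 points with an interval of about 4 to 22. A chi-square p-value alone does not convey that width. This step needs no assumption about covariates.

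**3. What adjustment adds.** The estimator is a logistic regression of readmission on allocation and baseline covariates. Each patient's risk is predicted under both allocations, and the difference is averaged over all patients.

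The documents give no figure for how well age and the Charlson index predict readmission, so this is an assumption, shown as a range. Trials were simulated with 139 per arm, marginal risks of 25% and 12%, and one normally distributed baseline score with the slope shown on the log-odds scale.

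| Assumed slope per SD | Power, chi-square | Power, adjusted | Gain (points) |
|---|---|---|---|
| 0.2 | 80.5% | 81.3% | 0.8 |
| 0.3 | 80.9% | 82.1% | 1.2 |
| 0.5 | 81.4% | 83.0% | 1.6 |
| 0.8 | 81.1% | 84.3% | 3.2 |

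Slopes of 0.3, 0.5 and 0.8 correspond to c-statistics of roughly 0.58, 0.64 and 0.70. With no treatment effect, rejection was 4.7 to 5.5%. Across the range the variance of the risk difference falls by about 0 to 9%. At the upper end the half-width becomes 9.0 × √0.91 = 8.6 points.

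**4. Two cautions on the table.** A simulated power near 80% from 4,000 runs has a standard error of √(0.8 × 0.2/4,000) = 0.6 point, so the smallest gains are close to simulation noise. Part of the gain also has nothing to do with covariates. In a separate run at slope 0.3, chi-square power was 80.0%, an unadjusted test with unpooled variance gave 80.5%, and the adjusted analysis gave 80.8%.

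**The case against.** The strongest case against is that nothing is wrong. The Sample size and Statistical analysis sections agree on outcome, test and α. The test is valid under randomisation and the stated power is delivered. A published article may also leave the effect measure that goes with a named test to the full analysis plan, and the percentages per arm would in any case let a reader work out the difference. All of this stands. The missing risk difference would not carry the point alone; the point is that a better method can be named from data already collected.

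Three stronger readings are tempting, and the documents do not support them.

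- *A reader might infer that the trial is underpowered or wastes power.* It is not underpowered: 139 per group gives 80.0% with the planned test. What is forgone is an extra, probably a small one.
- *A reader might infer that no effect estimate or adjustment is planned for cardiac readmission.* Unadjusted and adjusted hazard ratios with 95% CI are promised for time to first cardiac readmission, which is also listed as a primary outcome. The gap is confined to the percentage.
- *A reader might expect adjustment to remove chance imbalance.* It deals only with the covariates in the model, and only as far as they are prognostic.

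The objection to the size of the gain also stands in part. The eligibility criteria exclude patients whose other conditions affect cardiac prognosis or could interfere with training. That narrows the spread of the Charlson index, so the upper end of the assumed range is hard to support for age and Charlson alone.

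**Conclusion.** The point holds as a free improvement, not as a correction. The sized comparison has an unadjusted test and no named estimate or interval, while two usable covariates are recorded before allocation. The adjusted analysis would add about 1 to 3 points of power and reduce the variance of the risk difference by about 0 to 9%, at a type I error near 5%. The gain is more likely at the low end.

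These figures rest on an assumed slope of 0.2 to 0.8 per SD, on a single correctly specified score standing in for two covariates, and on the protocol's 25% and 12%. The benefit of an interval in percentage points depends on none of the covariate assumptions and is the firmer reason to make the change.

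**What to change.** In the Statistical analysis section, replace the sentence on the percentage readmitted with wording to this effect:

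*The percentage of patients readmitted for cardiac disease will be compared by logistic regression on allocated group, age and Charlson index, both as recorded at visit −1. The model will be standardised over all analysed patients to a risk difference with 95% CI, using a robust standard error. The unadjusted two-sided chi-square test will be reported as a sensitivity analysis.*

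The two covariates should be fixed now, before outcome data are seen. Variables first recorded at visit 1, such as ejection fraction and stress-test results, come after allocation and should not be added as baseline covariates.

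The cost is analysis wording only. No new data are needed and the sample size stays as it is. Age and Charlson index must be complete at visit −1.

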Despite the acknowledged benefits, however, CRPs are currently underused. According to the European Cardiac Rehabilitation Inventory Survey (2008)[7,8], of the 47.5% of the countries that answered the survey, 42.10% (including Belgium, Spain, and Italy) admitted ≤ 30% of eligible patients for phase II of CRP; 15.79% (Luxembourg, Sweden, UK) admitted >30-50% of eligible patients, and 15.79% (Germany, Iceland, Lithuania) admitted >50%. Data were unavailable for the remaining 26%.

Studies on post-MI survival, readmissions and physical rehabilitation date back to 1972 [9]. Most studies have found no significant differences in readmissions post-CRP but in 2005 one study concluded that global community CRP significantly reduced cardiac readmission rates [10]. In 2011, Heran et al. [11] published an updated systematic review of Jolliffe et al’s 2001 study, finding that exercise-based CRPs significantly reduced hospital admissions in the short term (<12 months), and in the same year Lawler [12] published the first meta-analysis showing a statistically significant reduction in MI recurrence with an exercise-based CRP post-MI (OR 0.53; 95% CI: 0.38 - 0.76). Moreover, the few studies of the issue do not focus on identifying the best exercise regimen for reducing readmissions, but on whether the intervention itself affects readmission rates. Only two of the studies presented statistically significant decreases in readmissions [10,12]. The value of readmission as an indicator of effectiveness of exercise lies in the fact that it is an indirect measure of clinical stability, so there is a clear need to study the relation between CRPs and readmission in MI patients.

The aim of this study is to evaluate the efficacy of a supervised exercise training program for reducing cardiac readmissions in patients with MI in the first year after hospital discharge. This study will also provide a detailed evaluation of the program’s effects on total mortality, functional capacity, quality of life and adherence to regular exercise. Our primary hypothesis is that a supervised exercise training program will significantly reduce the incidence of cardiac readmissions in patients with MI in the first year after hospital discharge. The secondary hypothesis is that patients in the intervention group will present significantly better functional capacity, better quality of life, and lower mortality rate.

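### Deaths before readmission are censored in the Kaplan-Meier analysis of a primary outcome, so the curves modestly overstate readmission risk and a readmission-only result cannot show whether deaths lie behind it

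*Protocol article*

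**What the plan says.** The primary outcome measures in the protocol article include the percentage of patients readmitted for cardiac disease within a year and the time to first such readmission (Primary outcome measures). The percentage is compared by a two-tailed chi-square test. The time is analysed by Kaplan-Meier, log-rank and Cox, all by intention to treat (Statistical analysis).

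On deaths, that section gives one rule: "The deaths occurring without hospitalization will be introduced in the survival analysis as censored data". It also says "Survival data will be presented graphically using the Kaplan-Meier method". It states no rule for how a patient who dies before any readmission enters the percentage.

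The secondary hypothesis in the Background is that intervention patients will have "better functional capacity, better quality of life, and lower mortality rate". All-cause death is a separate secondary outcome, and Table 1 has mortality recorded at visits 1 to 4.

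**The concern.** A patient who has died can no longer be readmitted. Ordinary censoring assumes that a censored patient would have gone on to face the same readmission risk as those still followed. For a death there is no such later risk. The Kaplan-Meier complement therefore describes a population in which death does not occur, whereas the other primary measure, the percentage readmitted, describes the patients as they are. The two will give different 12-month figures for what a reader takes to be the same quantity.

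The trial also expects the number of deaths to differ between arms. Any distortion need not be equal in the two curves, and the readmission result alone cannot tell a reader whether an arm with fewer readmissions simply had more patients die first. The Background treats readmission as an indirect measure of clinical stability. A death at home is not stability, yet it adds no event.

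This is not a detail left to an unseen analysis plan, because the article itself fixes the censoring rule.

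**Working it through.** **Step 1. The plan's own figure.** Inputs from Sample size: control 25%, intervention 12%, power 80%, "with a level of significance of 0.05", tested "through a two-tailed chi-square test for two independent samples". With pooled proportion (0.25 + 0.12)/2 = 0.185:

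n = [1.960 × √(2 × 0.185 × 0.815) + 0.842 × √(0.25 × 0.75 + 0.12 × 0.88)]² / 0.13² = 138.9, so 139 per arm.

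This is the stated number, and 139 × 1.05 gives the stated 146. The point does not rest on a sample-size error.

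**Step 2. How far Kaplan-Meier departs from the actual risk.** The article gives no mortality rate, so deaths before readmission are an assumption. Take constant cause-specific hazards over one year, with actual readmission risk I and death-first risk D. The total hazard is T = −ln(1 − I − D), the readmission hazard is λ = T × I/(I + D), and the Kaplan-Meier complement with deaths censored is 1 − exp(−λ).

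- Control, I = 25%, D = 5%: T = −ln(0.70) = 0.3567; λ = 0.3567 × 25/30 = 0.2972; 1 − KM = 25.7%.
- Intervention, I = 12%, D = 2%: T = −ln(0.86) = 0.1508; λ = 0.1508 × 12/14 = 0.1293; 1 − KM = 12.1%.
- Difference: 13.6 points on the curves, against 25 − 12 = 13.0 actual.

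Range for the control curve: D of 3%, 5% and 8% gives 25.4%, 25.7% and 26.2%.

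**Step 3. The same mismatch from the other side.** Suppose that 25% and 12% are the risks in the absence of death, and assume one-year mortality of 4% (control) and 2% (intervention). The Kaplan-Meier complement stays at 25.0% and 12.0%. The percentage actually readmitted, with deaths kept in the denominator, is 24.5% and 11.9%, a difference of 12.6 points. Power at 139 per arm is 78.3% instead of 80.0%. At 10% and 5% mortality the percentages are 23.8% and 11.7% (12.1 points, power 75.3%).

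**Step 4. What readmission alone cannot show.** Hold the actual readmission percentages at 25% and 12% and vary the assumed deaths before readmission:

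| Deaths first, control / intervention | Readmitted, difference | Readmitted or died, difference |
|---|---|---|
| 5% / 2% | 25 − 12 = 13 points | (25 + 5) − (12 + 2) = 16 points |
| 2% / 5% | 25 − 12 = 13 points | (25 + 2) − (12 + 5) = 10 points |

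The readmission result is identical in both rows. The last column is a different endpoint, so its distance from 13 is not a bias in the readmission estimate. It shows only what a supporting analysis would reveal.

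**The case against.** The case against is strong on several points, and most of it stands.

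- **Censoring is not scoring a success.** A reader might infer that the survival analysis counts a death as a year free of events. It does not: the patient leaves the risk set at death. The log-rank test and Cox hazard ratio remain valid for the cause-specific hazard of readmission. Only the absolute level of the Kaplan-Meier curve is affected.
- **The chi-square rule is not stated.** A reader might infer that the percentage analysis wrongly counts deaths as not readmitted. Intention to treat makes that reading natural, but the censoring sentence covers the survival analysis only. Such a percentage would not be wrong in any case. With complete follow-up it is the crude cumulative incidence, the same 12-month figure that an Aalen-Johansen curve gives.
- **Death is not hidden.** All-cause death is a secondary outcome, so a reader will see deaths by arm. It would be too much to say that the primary result is unreadable. But two separate totals give neither a correct readmission curve nor the share of patients alive and not readmitted.
- **Mortality may be low.** The exclusion of comorbidities that affect cardiac prognosis points that way, and the documents offer no figure.
- **A composite is a choice of estimand.** The stated hypothesis concerns cardiac readmission. This is why readmission or death belongs beside the primary result as a supporting analysis and not in its place.

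The objection does not remove the stated censoring rule, its use for the Kaplan-Meier curves of a primary outcome, or the trial's own expectation that mortality differs by arm.

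**Conclusion.** The point holds in a limited form. With deaths censored, one minus Kaplan-Meier overstates the actual readmission risk and will disagree with the percentage readmitted. Under the assumptions in Step 2 the excess is 0.7 points in the control arm and 0.1 in the intervention arm, so the apparent difference grows by 0.6 points. For the control curve alone, the excess runs from 0.4 to 1.2 points over the range tried. These figures rest on constant hazards and on assumed mortality.

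The direction depends on which summary is read. If mortality is lower with training, as hypothesised, the Kaplan-Meier curves slightly enlarge the apparent benefit. In the percentage readmitted, the extra survivors remain at risk and the difference is slightly smaller. It would therefore be wrong to say that the plan simply understates, or simply overstates, the effect.

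The hypothesis tests and the sample size are not undermined. What remains is a curve that does not estimate what readers will take from it, and a readmission-only result that cannot separate fewer readmissions from more early deaths.

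**What to change.** Change the Statistical analysis section as follows:

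1. Keep the Cox model and log-rank test, and label the hazard ratio as cause-specific for cardiac readmission.
2. Replace the Kaplan-Meier readmission curves with Aalen-Johansen cumulative incidence curves that treat any death before cardiac readmission as a competing event. The wording should also cover deaths during or after a non-cardiac admission, which the present rule on deaths without hospitalization leaves unclear.
3. State that patients who die before readmission stay in the denominator of the percentage readmitted.
4. Pre-specify one supporting analysis of cardiac readmission or all-cause death, as a 12-month proportion and as time to first event, reported beside the primary result.

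The cost is a few sentences of analysis wording and one more analysis to report. Deaths are already collected at visits 1 to 4, and the primary endpoint and sample size are unchanged. The wording should be settled before results by arm are seen, so that the choice is not made after the fact.
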